Stable cephalic presentation with Bishop score <6 CTG classified as normal according to the antepartal Swedish Society of Obstetrics and Gynaecology (Svensk Förening för Obstetrik och Gynekologi, SFOG) criteria (www.ctgutbildning.se)	Small for gestational age (SGA) defined as <2 SD and in case of diabetes either large for gestational age (LGA) defined as >2 SD according to Marsal *et al*^55^ or suspected growth acceleration (according to the hospital’s guidelines). If the criteria outlined below are not met in their respective situation, the patient shall be excluded from the study: In case of late term ≥41+0 to 41+6 weeks, abdominal ultrasound will be performed and mean abdominal diameter (MAD) must be ≥110 mm. In case MAD <110 mm, the foetal weight will be estimated to exclude SGA fetus and if SGA <2 SD according to Marsal *et al*^55^, the patient should be excluded In case of dietary or metformin-treated gestational diabetes, foetal weight needs to be or have been estimated by abdominal ultrasound within the last 3 weeks before induction and the result needs to be within normal range In case of stable hypertension, foetal weight needs to be estimated by abdominal ultrasound within the last 2 weeks before induction and showing no SGA/IUGR fetus In case of indication for induction being prolonged latent phase, maternal age, mild intrahepatic cholestasis, pelvic girdle pain, PROM or psychosocial, fundal height measurement according to the Swedish reference curves must be normal. In case of not-normal fundal height measurement, foetal weight estimation must be performed and showing no SGA/IUGR For all other indications, foetal weight is estimated by abdominal ultrasound at the discretion of the investigator. Oligohydramniosis: deepest vertical pocket <20 mm or amniotic fluid index <50 mm Polyhydramniosis: amniotic fluid index >250 mm or single deepest pocket >80 mm Maternal pyrexia >38°C Known low-lying placenta (less than 20 mm from internal os measured by ultrasound) Regarding premature rupture of membranes (PROM): PROM is exclusion criteria for catheter method PROM is exclusion criteria for misoprostol if: Time point for confirmed PROM with timepoint for PROM as indicated by the woman >48 hours Known colonisation with group B streptococci or previous pregnancy complication linked to group B streptococci^48^
Based on observation the first 45 min after start of induction	

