#### Induction of labour

IOL is initiated in the hospital and performed using methods applied in clinical routine: mechanical methods—double balloon catheter (Cook Cervical Ripening Balloon with Stylet, Cook Medical, [name]) or single balloon catheter (see online supplemental table 1 for approved models marked as study product)—or the medical method (oral tablets of 25 µg misoprostol; Angusta, Norgine BV, Amsterdam, Netherlands). The method of IOL is chosen depending on the woman’s informed choice, local practice and the physician’s advice, and following the guidelines from the Swedish Society of Obstetrics and Gynaecology (SFOG).^28^ However, in the case of prelabour rupture of the membranes (PROM), misoprostol is the only choice. The double balloon catheter (Cook) is administered as specified by the manufacturer. Similarly, the single balloon catheter is placed by speculum/amnioscope or digitally; whereafter, the balloon is filled with up to 50 mL saline solution. A dose of 25 µg oral misoprostol is taken no closer than 2 hours apart with a maximum of eight doses per 24 hours as specified by the manufacturer.

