#### Randomisation

After the balloon catheter has been placed or the woman has taken the first dose of oral misoprostol, the woman is observed for 45 min. For women who received a balloon catheter, a CTG is registered after insertion, before randomisation, see figure 2. For women who received the first dose of oral misoprostol, an additional CTG is only registered if indicated, for example, start of contractions. For exclusion criteria after initiation of IOL, see table 1. Following inclusion, but before randomisation, participating women and partners complete the first electronic questionnaire.

Randomisation is conducted online via a module linked to the SPR, accessible through a computer using a personal staff identification card and two-factor authentication. The module includes both the randomisation module and the electronic case report form (eCRF). Randomisation is performed by optimal allocation (minimisation) per study site considering (1) indication for IOL (PROM – no PROM), (2) parity (nulliparous – parous) and (3) method of IOL (balloon catheter – oral misoprostol). At study completion, allocation is 1:1 with maximum difference of two patients between the two randomised groups within each centre. Blinding is not deemed feasible for neither patient, partner, care provider, nor clinical research staff. The approach to not randomise until after an initial observational period ensures that the choice of IOL method and subsequent monitoring is not influenced by known group allocation and hence, minimises difference in intention to treat (ITT) and per-protocol populations.

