#### Procedures and follow-up

The trial intervention is IOL outside of a hospital setting. For IOL due to PROM, the method of cervical ripening and whether the setting will be outpatient or inpatient is set for the first 24 hours. For IOL due to other indications, these details are specified for the first 48 hours. Thereafter, all participants are treated according to clinical routine at their hospital. Usually, IOL will proceed with oxytocin infusion in case of PROM and amniotomy and subsequent oxytocin infusion in women with intact membranes.^29^

Women randomised to inpatient IOL are monitored according to local clinical routine. Women randomised to outpatient IOL return home or to a patient hotel defined as a facility without access to medical surveillance. Participants receive oral and written information on how to proceed with IOL, when and whom to call and when to return to the hospital. Women have access to a 24/7 telephone line staffed by qualified midwives based at the maternity hospital. Women randomised to outpatient IOL receive detailed oral and written instructions to contact the hospital (and refrain from further intake of oral misoprostol) at start of contractions, in case of PROM (if PROM was not the indication for IOL), when the balloon catheter is expelled, sudden change/decrease in foetal movements, vaginal bleeding, abdominal pain, fever and/or feeling unwell, and in case of IOL due to PROM: any change in amniotic fluid colour. These women are counselled to come to the hospital for a clinical evaluation. Women are also encouraged to call in case they feel unsure about anything.

If labour does not start and no complication occurs, women in the outpatient group return for assessment after 24 hours (12 hours in case of IOL with a double balloon (Cook) catheter due to conformité européenne (CE) marking for 12 hours use only) for clinical assessment including vaginal examination of the cervix, blood pressure and CTG. Women induced due to PROM are admitted to the hospital at the latest 24 hours after start of IOL. Women induced due to other indications and a normal assessment may return home/to the patient hotel for continued cervical ripening for another 24 hours if needed.

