Three interim safety analyses have been prespecified. The first safety analysis after the first 1000 randomised women had given birth did not prompt any changes in the study protocol. Further analyses are planned after 3500 and 6000 randomised women have given birth. Patient groups that are studied in subanalyses during the safety analyses are primiparous and multiparous women, women induced due to PROM or other indications, and women induced primarily with balloon catheter or oral misoprostol. Results are only available for the DSMB; whereas, the sponsor, steering group and statistician remain blinded. According to the DSMB charter, due to the non-inferiority design, the study should not be stopped due to a positive difference in the primary composite endpoint and neither for futility (conditional power). The main aim is to assess safety for the women and foetuses/children involved in the study. If deemed necessary, the DSMB will make recommendations to the sponsor and steering group regarding continuation, modification or termination of any or all arms of the study. All changes to the study protocol and conduction of the study must be approved by the Swedish Ethical Review Authority, the Swedish Medical Products Agency (medical technical device) and the European Medicines Agency (investigational medical product).

Study participants are covered by the Swedish Patient Injury Act and the Pharmaceutical Insurance provided by the healthcare regions.

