#### Data analyses

The final statistical analysis plan (SAP) will be set prior to data lock. All main analyses will be performed according to ITT, and complementary analyses will be performed on the per-protocol population. The statistician performing the analyses will be blinded to allocation and primary IOL method.

For comparison between the two allocation groups, Fisher’s exact test will be used for dichotomous variables, Fisher’s non-parametric permutation test for continuous variables, Mantel-Haenszel χ² test for ordered categorical variables and Pearson’s χ² test for non-ordered categorical variables. For all comparisons between the two groups, regarding dichotomous and continuous variables, mean differences with 95% CI will be calculated.

For the primary outcome variable and other dichotomous outcome variables, multivariable binary regression will be used for the adjustment. For continuous variables, analysis of covariance (ANCOVA) will be used for the adjustment.

For dichotomous variables, risk difference with 95% CI and risk ratio with 95% CI will be calculated between the two groups and 95% CIs for the estimated proportions. The distribution of continuous variables as well as change in continuous variables will be given as mean, SD, median, minimum, maximum, and first and third quartiles. Categorical variables will be given as number and proportion. Exploratory analyses will be performed on subgroups stratified for parity (primiparous vs multiparous women), initial method of IOL (balloon catheter vs oral misoprostol), Bishop score in women without PROM (<3 versus ≥3), indication for IOL (PROM vs other than PROM) and reported travel time to the hospital (<30 min and ≥30 min).

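### All eligible women induced for PROM are in the misoprostol group, so comparing the setting effect between the balloon and misoprostol subgroups mixes method with PROM; a three-stratum table would separate them

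*Protocol article*

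**What the plan says.** **Eligibility and method.** Table 1 of the protocol article states "PROM is exclusion criteria for catheter method". The section Induction of labour adds that "in the case of prelabour rupture of the membranes (PROM), misoprostol is the only choice". For other women, "The method of IOL is chosen depending on the woman’s informed choice, local practice and the physician’s advice", so method is not randomised.

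**Intervention.** Under Procedures and follow-up, for women induced because of PROM the method and "whether the setting will be outpatient or inpatient is set for the first 24 hours". For other indications the period is 48 hours.

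**Randomisation.** Minimisation per site uses "indication for IOL (PROM – no PROM), (2) parity (nulliparous – parous) and (3) method of IOL". The section also says "At study completion, allocation is 1:1 with maximum difference of two patients" between the groups within each centre.

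**Final analysis.** Data analyses names exploratory subgroups by parity, method, Bishop score, indication (PROM or other) and travel time. The relevant part reads "initial method of IOL (balloon catheter vs oral misoprostol), Bishop score in women without PROM (<3 versus ≥3"). Method and indication are separate splits, and only Bishop score is restricted to women without PROM.

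**Safety analyses.** Study monitoring and safety gives the DSMB sub-analyses by parity, by PROM or other indication, and by method ("women induced primarily with balloon catheter or oral misoprostol"). The DSMB may recommend that any or all arms continue, change or stop.

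**Sample size and power.** Power calculation sizes the efficacy assessment at 2119 women per arm for each method. The strengths and limitations list says that safety cannot be assessed with adequate power for each method separately.

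**The concern.** The cell for balloon with PROM is empty by design. Balancing settings within PROM and within method does not fill it. Every difference between PROM and other women in what outpatient care does is therefore carried into the contrast between the method subgroups.

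Such a difference is plausible on the document's own terms. The assigned setting lasts half as long in PROM women, and the safety composite includes neonatal sepsis and pneumonia.

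What is at stake is interpretation. An outpatient excess confined to PROM women would show as a worse outpatient result on misoprostol than on balloon. Conversely, a null effect in PROM women would dilute a real effect in the other misoprostol women. The DSMB sees the same two one-way splits and can make recommendations by arm. The two methods are also approved separately, as a medication arm and a device arm, so a reading by method is to be expected.

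**Working it through.** **1. The plan's own figures.** I used non-inferiority for a risk difference with the Farrington-Manning restricted variance: n per arm = [(z(1−α)·s0 + z(power)·s1) / distance to margin]², where s0 and s1 are the standard-deviation terms at the margin and under the assumed rates.
- Safety (2.8% v 2.3%, margin 1.5 points, two-sided 95.7% CI, 80% power): [(2.0237 × 0.2284 + 0.8416 × 0.2229) / 0.010]² gives 4223 per arm, 8446 in total. 8446 / 0.95 = 8890.5, so 8891, as stated.
- Efficacy (90% v 88%, margin 1.5 points, two-sided 99.3% CI): [(2.6968 × 0.4442 + 0.8416 × 0.4423) / 0.035]² gives 2013 per arm. 2013 / 0.95 = 2118.9, so 2119, as stated.

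The sample sizes are sound, and this point does not touch them.

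**2. The cross-table fixed by eligibility.**

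| | No PROM | PROM |
|---|---|---|
| Balloon | present, 48 h setting | empty by design |
| Misoprostol | present, 48 h setting | present, 24 h setting |

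The planned method split compares row totals. The planned indication split compares column totals. Neither shows misoprostol without PROM as a stratum of its own.

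**3. Size of the false contrast.** Let q be the PROM share of the misoprostol group, d the setting effect without PROM (the same for both methods) and d + e the effect with PROM.
- Balloon effect: d
- Misoprostol effect: (1 − q)·d + q·(d + e) = d + q·e
- Contrast with no true method effect: q·e

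The documents give neither q nor e. With d = 0.5 points (the planned 2.8% − 2.3%) and assumed q and e:

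| q | e = 1 point | e = 2 points |
|---|---|---|
| 10% | 0.1 | 0.2 |
| 30% | 0.3 | 0.6 |
| 50% | 0.5 | 1.0 |

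At the top corner misoprostol shows 1.5 points against 0.5 for balloon. A harsher assumption of e = 3 with q = 40% gives 0.4 × 3 = 1.2.

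**4. Does covariate adjustment remove it?** I took q = 30%, e = 2, an even method split, and inpatient risk of 2.3% without PROM and 3.3% with PROM (the extra point is assumed). The setting-by-method coefficient is then:
- unadjusted: 0.6 points
- with PROM as a main effect: 0.6 points
- with a setting-by-PROM term: 0.0

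A PROM main effect shifts both settings equally, so it cannot absorb a difference in setting effect.

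**5. Precision of the between-method contrast.** Assume an even method split and the planned rates. Analysed women per method and setting: 8446 / 4 = 2111.5. Variance of one risk difference: (0.028 × 0.972 + 0.023 × 0.977) / 2111.5 = 0.04969 / 2111.5. The 95% half-width of the difference between two such risk differences is 1.96 × √(2 × 0.04969 / 2111.5) = 0.0134, about 1.3 points.

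**6. Cost of leaving out PROM women.** The interval for the misoprostol stratum widens by 1/√(1 − q): 1/√0.8 = 1.12 at q = 20% and 1/√0.6 = 1.29 at q = 40%, so about 12% to 29%.

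**The case against.** The strongest reply is that the information is already there. Because balloon with PROM is empty, the events and denominators for misoprostol without PROM are the all-misoprostol counts minus the PROM counts in each setting. The DSMB also sees the PROM split beside the method split, so a PROM signal would appear under its own name. This stands for unadjusted counts. But the listed splits report neither the estimate nor the interval for that stratum, and subtraction does not yield an adjusted result.

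Second, these are exploratory subgroups, safety power by method is disclaimed, and the analysis plan and DSMB charter may cross the factors. It is right that nothing in the article forbids this. The article does, however, fix the splits as one-way in two places, and it restricts Bishop score to women without PROM without doing the same for method.

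Third, the illustrated contrasts lie within the half-width of about 1.3 points, and the 1.5-point margin applies to the overall setting effect, not to a contrast between methods. Both are correct, so the illustrated sizes should not be judged against that margin.

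A reader might infer three stronger things that the documents do not support:
- That the method-specific results are invalid. Outpatient versus inpatient within each method is randomised, with both factors in the minimisation.
- That the primary non-inferiority conclusions are at risk. They do not use the method contrast.
- That restricting to women without PROM gives a clean comparison of methods. Method is chosen by woman, site and physician, so other confounding remains.

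**Conclusion.** The point holds as a limited one about interpretation. Any comparison of the setting effect between the balloon and misoprostol subgroups, in the final analysis or the DSMB tables, confounds method with PROM. This follows from the eligibility rules and needs no assumption. It produces a false contrast only to the extent that the setting effect differs between PROM and other women.

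The size cannot be derived from the documents. The range of 0.1 to 1.0 percentage points rests on an assumed PROM share of 10% to 50% and an assumed extra effect of 1 to 2 points, and is illustrative only. "PROM is exclusion criteria for catheter method" also does not mean that every woman with PROM is randomised to a setting on misoprostol: Table 1 excludes some altogether, by time since rupture or because of group B streptococci. The statement therefore covers eligible women induced for PROM.

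This is a worthwhile, inexpensive improvement, not a defect in the primary inference.

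**What to change.** In the analysis plan and the DSMB tables:
- Report the setting effect in three strata: balloon without PROM, misoprostol without PROM, misoprostol with PROM.
- Base any comparison of setting effect between methods on the two strata without PROM, or on a model that includes a setting-by-PROM term as well as setting-by-method. A PROM main effect alone is not enough.
- Keep the all-misoprostol result as planned, including the efficacy assessment by method sized at 2119 per arm.
- State that method is not randomised, so this removes the structural confounding by PROM but not all confounding.

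Both factors are minimisation factors and already recorded, so no new data, sample size or change in conduct is needed. The timing allows it: 2172 women had been randomised by 10 July 2025, the safety analyses at 3500 and 6000 births are described as still planned, and the analysis plan is to be set before data lock. The price is the wider interval for the misoprostol stratum used in the method contrast, about 12% to 29% if the PROM share is 20% to 40%.

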### Power calculation

Non-inferiority will be tested with a two-sided 95% CI and 80% power. Calculating with 2.8% (based on data from the SPR 2014–2018^5^) for the primary composite outcome in outpatients and 2.3% in inpatients and a 5% drop-out rate, 8891 women need to be randomised to achieve a probability ≥0.80 that the upper limit of a two-sided 95.7% CI for the difference in primary outcome will be less than the non-inferiority margin 1.5%. The vaginal delivery rate was 88% in a group of women fulfilling the eligibility criteria (SPR, 2014–2018^5^). Assuming a vaginal delivery rate of 90% in the outpatient arm, calculating with 80% power, a two-sided 99.3% CI, a non-inferiority margin of 1.5% and a 5% drop-out rate, 2119 women need to be randomised to each arm induced with either balloon catheter or oral misoprostol to assess efficacy of either method in the different IOL settings.

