For the health economy analysis, the primary analysis of effectiveness will be comparable to the composite outcome defined as primary outcome.^48^ If non-inferiority is established in the primary analyses, a simpler cost-minimisation analysis will be conducted, that is, only analysing differences in economic costs (and not in relation to the clinical outcomes). All analyses will focus on differences in means between costs and between clinical outcomes. Since cost data are typically non-normal, sampling uncertainty on differences in costs and cost-effectiveness will be assessed by non-parametric bootstrapping.^48^ Applying a simulation model, cost effectiveness for a longer time horizon will be assessed by extrapolation. To do so, associations between neonatal and maternal morbidity and health outcomes later in life will be estimated based on available epidemiologic literature.

For the qualitative studies, data analysis will be conducted by either phenomenology with a lifeworld approach^49^ or content analysis.^43 50^

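### Establishing non-inferiority does not justify the planned switch to a costs-only economic analysis, and the rule conflicts with the sentences that follow it

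*Protocol article*

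**What the plan says.** The health-economic paragraph under Data analyses starts from an effect measure: "the primary analysis of effectiveness will be comparable to the composite outcome defined as primary outcome". It then sets a condition: "If non-inferiority is established in the primary analyses, a simpler cost-minimisation analysis will be conducted, that is, only analysing differences in economic costs", and adds in brackets "and not in relation to the clinical outcomes".

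Three statements follow, and none is tied to the non-inferiority result:
- "All analyses will focus on differences in means between costs and between clinical outcomes"
- "sampling uncertainty on differences in costs and cost-effectiveness will be assessed by non-parametric bootstrapping"
- "Applying a simulation model, cost effectiveness for a longer time horizon will be assessed by extrapolation", for which "associations between neonatal and maternal morbidity and health outcomes later in life will be estimated based on available epidemiologic literature"

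The Power calculation section sets the safety margin at 1.5 percentage points, judged by the upper limit of a two-sided 95.7% CI. It assumes 2.8% "for the primary composite outcome in outpatients and 2.3% in inpatients", which is a planned excess of 0.5 points in the outpatient arm.

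**The concern.** Cost-minimisation compares costs alone, so its conclusion carries over to a decision only if the two settings give the same outcomes. Non-inferiority does not show that. It puts an upper bound on the harm, and the bound here is wide relative to the baseline: 1.5 / 2.3 is about 65% of the assumed inpatient rate. The sample size is itself built on outpatients doing somewhat worse, so the event that triggers the switch is the expected result in a scenario where outcomes are assumed to differ.

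What is at stake is the usefulness of the economic result. The Introduction faults earlier economic evaluations because their source studies were not powered for the most severe outcomes. The Discussion gives the economic analyses a central role in deciding whether outpatient induction becomes routine. Setting the effect estimate and its uncertainty aside once non-inferiority is met would discard information that this trial is large enough to supply.

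**Working it through.** **Inputs (Power calculation; allocation from Randomisation).** Outpatient rate 2.8%, inpatient rate 2.3%, margin 1.5 points, two-sided 95.7% CI (one-sided 0.0215, z = 2.0237), power 0.80 (z = 0.8416), 5% dropout, 1:1 allocation, 8891 randomised.

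**1. Reproduce the plan's figure.** Farrington-Manning test for a risk difference:
- n per arm = [2.0237·√V0 + 0.8416·√V1]² / (0.015 − 0.005)²
- V1 = 0.028·0.972 + 0.023·0.977 = 0.04969
- V0 uses the restricted rates at a difference of 1.5 points (3.436% and 1.936%): 0.05217
- n = [2.0237·0.22840 + 0.8416·0.22291]² / 0.0001 = 4222.6, rounded up to 4223
- Randomised = 2·4223 / 0.95 = 8890.5, rounded up to 8891, an exact match

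The simpler unpooled formula gives 4080 per arm and 8590 randomised. The steps below use 4223 evaluable women per arm.

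**2. How likely is the trigger when outpatients are 0.5 points worse?**
- SE = √(0.04969 / 4223) = 0.00343
- P(pass) = Φ(0.010 / 0.00343 − 2.0237) = Φ(0.892) = 0.81 by normal approximation, in line with the planned 0.80
- Expected excess = 0.005 × 4223, about 21 composite events per arm, or 5 per 1,000 outpatient inductions

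**3. How large an observed excess still passes?** Fix inpatients at 2.30% and solve d + 2.0237·SE(d) = 0.015, where SE(d) is computed at the observed rates:
- d = 0.0079, that is 3.09% against 2.30%
- SE = √[(0.0309·0.9691 + 0.023·0.977) / 4223] = 0.00352, half-width 0.00713
- 95.7% CI: 0.07 to 1.50 points
- Risk ratio 3.09 / 2.30, about 1.34; about 33 extra events per arm

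So the trial can declare non-inferiority while the interval lies wholly above zero.

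**4. How likely is that combination?** At a true excess of 0.5 points, with SE 0.00343 and half-width 0.00694, the observed difference must lie between 0.694 and 1.5 − 0.694 = 0.806 points. The probability is Φ(0.892) − Φ(0.566), about 0.10. (The limit of 0.806 here keeps the SE at the planning rates; step 3 recomputes it at the observed rates, which gives 0.79.)

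**5. Does the text fit together?** The conditional rule confines the analysis to costs. The sentence directly after it says that every analysis looks at differences in costs and in clinical outcomes. The bootstrap is to cover cost-effectiveness, and the longer-horizon model needs morbidity as an input. If non-inferiority is established, a reader cannot tell which of these analyses still run.

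**The case against.** The strongest reply is that the rule does not strip clinical outcomes from the economic plan. The three sentences after it are unconditional, so effects and their uncertainty may still be analysed. That stands as a limit on the point: a reader might infer that the whole economic evaluation ignores outcomes once non-inferiority is met, and the article does not say so. It does not rescue the rule, because those sentences contradict it.

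A reader might also infer that 5 extra events per 1,000 would count for nothing. The documents do not support this. The Health economic outcome section lists child and maternal outcomes, hospital time, mode of delivery, unscheduled visits and readmissions, so extra morbidity can enter as resource use. What a costs-only comparison leaves out is the health value of the events beyond their cost. Nor does the article call the cost-minimisation its main economic result or state that the arms are equal; equality is what the method presupposes.

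A charge of data-driven analysis would be too strong, since the trigger is a published rule tied to a prespecified test. A claim of bias towards outpatient induction of some given size cannot be made either: the 0.5-point excess is a planning assumption, and the documents do not say how events would be valued.

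Finally, the 80% refers to safety alone. The rule speaks of primary analyses in the plural and there are two primary outcomes. If both must pass, the switch is triggered at most as often as the safety comparison passes.

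**Conclusion.** The point holds for the conditional rule. The article prescribes a costs-only analysis after a result that bounds the excess below 1.5 points without showing equal outcomes. On the plan's own rates the safety comparison passes about 80% of the time with outpatients 0.5 points worse, and an observed excess of up to about 0.79 points can pass with an interval that excludes zero. These figures assume 4223 evaluable women per arm, inpatients at 2.3% and a normal approximation.

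The rule is stated outright, so it is not a detail left to the statistical analysis plan, and it conflicts with the rest of its own paragraph. The consequence is confined to a secondary analysis. The primary tests and the sample size are untouched. It should be corrected before the analysis plan is final.

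**What to change.** Remove the conditional switch. State that incremental cost and the difference in the composite will be estimated jointly, with the bootstrap already planned, whatever the non-inferiority result; for example as incremental cost per composite event avoided, with an acceptability curve. Report the cost-only difference as a supplementary component. Then reword the paragraph so that the scope sentence, the bootstrap and the longer-horizon model all describe the same set of analyses.

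The cost is a little more analysis work. No extra participants or data are needed, because the effect data are already collected. The article says that the final analysis plan will be set before data lock and that recruitment runs to the end of 2028, so the change can be made before the final results are known.
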